In sum, there is an urgent need to improve the quality of children’s dietary intake. Optimizing school meals within the NSLP can have a significant public health impact. Tremendous resources have been invested in school salad bars as a means to increase FV intake, yet it is not known if they achieve this goal. By randomly selecting schools receiving salad bars, matching them with those serving pre-portioned FV only, and conducting a comprehensive, longitudinal evaluation that includes objective, validated assessments of dietary intake, this investigation will address these critical gaps. Specifically, this study will identify: (1) how salad bars impact dietary consumption in NSLP lunches, and (2) consequences of, and barriers and facilitators associated with, salad bar implementation. It will also examine the potential moderating role of the school-level sociodemographic factors of percent high obesity risk racial/ethnic minority students and Title I status on dietary consumption, and salad bar implementation barriers and facilitators. In the current study, all FVs on the salad bars will be fresh and *replace* all fixed portion FVs on the serving line. All schools will operate under a policy requiring students to take at least one FV serving [44]. This will allow examination of the independent and combined impact of variety and choice, two mechanisms with potential to increase FV intake, within the NSLP. We hypothesize that schools with salad bars will manifest greater increases in both FV selection and consumption, and decreases in FV waste, compared with schools without salad bars. In addition, we hypothesize that schools with salad bars will have greater improvements in dietary quality and reductions in total energy intake at lunch, compared with schools without salad bars.

Data from this trial will yield some of the clearest evidence related to salad bars to date, providing a strong evidence base to evaluate school nutrition policies designed to enhance dietary intake and reduce health disparities within the NSLP. Results can guide resource allocation and inform targeted interventions and policies designed to reduce obesity.

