### Design

Twelve pairs of matched schools will be randomly selected: half will receive a salad bar (Intervention; replacing all other FVs) and half will only serve pre-portioned FVs, standard under the NSLP (Control). Thus, groups will have different FV presentation methods; however all schools will be operating under a policy requiring students to take at least one FV serving [44]. In contrast to prior salad bar research, [28] salad bars in the current study will replace all other FVs on the lunch line, and students can select their entire meal from the salad bar. This implementation model facilitates a more rigorous comparison between schools with and without salad bars than that conducted in prior research. Schools will be matched on Title I status (a proxy for socioeconomic status [SES]) and percent of racial/ethnic minority students based on higher obesity risk. Dietary intake at lunch will be objectively assessed in each pair of schools, prior to (baseline), and 4–6 weeks after salad bars are installed (post), resulting in ~ 14,160 lunch observations throughout the study duration. The primary dependent variable of interest is change in FV intake, assessed using digital imagery plate waste methods. Cafeteria sales and NSLP participation data will also be examined to assess the potential impact of salad bars on these critical revenue sources. Finally, we will assess implementation practices and cafeteria personnel’s perspectives, to identify barriers and facilitators to salad bars and inform sustainability efforts.

Prior to random selection, each school will be assigned to one of 4 categories based on sociodemographic variables. We used information from schools that received salad bars in the first 2 years of the district’s program (prior to the current study) to develop matching procedures. Matching was based on: 1) Title I status, which includes % free and reduced-price lunch, and 2) % of students from racial/ethnic backgrounds at higher risk of obesity (Native American, African American/Black, Latinx, Native Hawaiian/Pacific Islander, more than one race). Four categories of schools resulted: A = < 40% minoritized AND not Title I; B = 40–60% minoritized AND not Title I; C = 40–60% minoritized AND Title I; and D = > 60% minoritized AND Title I. Matching procedures were then applied to the remaining 91 schools, demonstrating that each category has adequate numbers of schools in each year of this study to successfully execute the proposed aims.

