### FV selection

Raters will note which items were available and selected, including number and types of FVs (coded with a location). Vegetables will be categorized as dark green, red/orange, legumes, starchy, and other, consistent with USDA/NSLP [44]. Fruit is defined as whole fruit (not juice). *Variety* will be scored as the number of different types of FVs and as the number of different categories of vegetables the student selected. *Location* (salad bar, lunch line, or point of sale) and serving type (self-serve, pre-portioned) of each FV will be obtained from photographs of the lunch line.

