## Statistical analyses

### Power analysis

Power and effect size of the multilevel models that will be used to analyze the variety of outcomes in our cluster RCT are a function of a number of parameters: (1) the number of clusters (J = 16 independent schools [8 Intervention and 8 Control]), (2) the cluster size (*n* = 295 lunches per school), and (3) the ICC (estimated as 0.01, 0.05, and a much more conservative 0.10), which takes into account the correlated nature of our data and is the ratio of variability between clusters to the total variability [66]. Optimal Design Plus Empirical Evidence v3.01 software [67] was used to calculate the minimum detectable effect size given the parameters above, α = 0.05, and a desired power of 80%. For ICCs of 0.01, 0.05, and 0.10, we have 80% power to detect small to medium effect sizes of 0.17, 0.35, and 0.48, respectively. Thus, our proposed sample of 14,160 observations will be more than adequate to evaluate the study aims.

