### Analyses

Prior to analyses, distributions of all measures will be examined. Contingency tables and frequency distributions will be evaluated (for categorical and continuous variables, respectively), and transformations considered. Outliers will be checked for errors before being used in analyses. Sex differences will be assessed for all outcomes; if significant differences are found, analyses outlined below will be stratified by sex. All tests will be 2-sided at α = 0.05 level, corrected for multiple comparisons, and conducted in SAS v9.3.

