Analyses are dictated by the cluster RCT study design. Data are hierarchical, gathered in multiple levels. The first level of measurement is from students, clustered within schools, the second level of measurement. We are measuring consumption based on students, yet their treatment assignment is defined by the school’s assignment. This nested structure must be considered in analyses as the assignment of intervention to the schools can result in students within schools being positively correlated for the outcomes. Without accounting for correlated nature of the data, Type 1 error rate for the intervention effect might be inflated and the significance of the study findings misinterpreted. Multilevel Linear Modeling (MLM) is a type of regression used to analyze nested data as it can accommodate fixed and random effects and correlated observations within units of assignment (schools). SAS PROC MIXED (for continuous variables) and PROC GLIMMIX (for dichotomous and polytomous data) have MLM applications which take into account random effects and correlated observations and will be used in these analyses. Potential covariates include grade, NSLP participation, and month of assessment, and factors related to the school cafeteria environment that might differ between schools (e.g., lunch duration), where appropriate. Using these models, we will evaluate differences between Intervention and Controls schools in types and variety of FVs and categories of vegetables selected, and subsequent consumption (% consumed/wasted) at baseline and 4–6 weeks after salad bars are installed. Variety will be recorded as the number of different types of FVs selected for each meal, and the number of categories of vegetables (ranging from 1 to 5; corresponding with USDA categorization) [44]. For the primary outcome (FV consumption), plate waste ratings will be calculated for fruits, vegetables, each specific FV category, and also averaged across FVs. We will also evaluate the effect of location of FVs (salad bar, lunch line, or at the point of sale) and serving type (self-serve, pre-portioned) of each item on FV selection and consumption to inform best implementation practices.

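### The primary outcome is not tied to one score or unit, and the stated 80% power holds only for a single uncorrected test, although all tests are to be corrected

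*Protocol article*

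**What the plan says.** The Design section is singular: "The primary dependent variable of interest is change in FV intake, assessed using digital imagery plate waste methods". It gives no unit.

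The Analyses section takes up the primary outcome again in these words: "For the primary outcome (FV consumption), plate waste ratings will be calculated for fruits, vegetables, each specific FV category, and also averaged across FVs". The FV selection section supplies the categories: "Vegetables will be categorized as dark green, red/orange, legumes, starchy, and other". The models are described as comparing "subsequent consumption (% consumed/wasted) at baseline and 4–6 weeks after salad bars are installed", so the metric there is a percentage of what was served.

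The only multiplicity rule is in the Analyses section: "All tests will be 2-sided at α = 0.05 level, corrected for multiple comparisons, and conducted in SAS v9.3". It names no method and no family, and it does not set the primary test apart.

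The Power analysis section uses "α = 0.05, and a desired power of 80" percent, with "16 independent schools [8 Intervention and 8 Control"], 295 lunches per school and intraclass correlations (ICCs) of 0.01, 0.05 and 0.10. It reports detectable standardised effects of 0.17, 0.35 and 0.48 and judges the sample more than adequate.

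The Background section hypothesises that "schools with salad bars will manifest greater increases in both FV selection and consumption, and decreases in FV waste", and adds diet quality and energy intake. It does not label any of these as primary.

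**The concern.** Two things do not fit together.

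First, the Design section's single construct is never linked to one of the scores in the Analyses section. The likeliest match is the average across FVs, but no sentence says so, and intake is not the same quantity as percent consumed. The Background section reports that in an earlier two-school study self-served portions were smaller and mean FV intake fell by 0.65 cups. When portions shrink, percent consumed can rise while the amount eaten falls. An average of percentages and a total amount could then answer the trial's question differently.

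Second, the sample size is justified for one test at 0.05, while the testing rule corrects every test. If the primary test shares a correction with anything else, the stated power is not the power of the planned analysis.

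At stake is whether a result on salad bars and FV intake can be read against a rule fixed in advance, and whether a null result comes from a test with the power claimed for it.

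**Working it through.** **Inputs.** J = 16 schools (8 per arm), n = 295 lunches per school, ICC = 0.01, 0.05, 0.10, two-sided α = 0.05, power 80%; all from the Power analysis section.

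**Step 1: reproduce the printed detectable effects.** For a two-level cluster design with outcome SD 1,

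SE = √[4 × (ICC + (1 − ICC)/n) / J], with J − 2 = 14 degrees of freedom.

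- ICC 0.01: √[4 × (0.01 + 0.99/295)/16] = 0.0578
- ICC 0.05: √[4 × (0.05 + 0.95/295)/16] = 0.1153
- ICC 0.10: √[4 × (0.10 + 0.90/295)/16] = 0.1605

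Solving the non-central F (1, 14 df) for 80% power gives 0.174, 0.348 and 0.484, about 3.01 × SE in each case. The printed values are 0.17, 0.35 and 0.48. Power at the printed values is 78.1%, 80.5% and 79.4%. A normal approximation gives 0.162, 0.323 and 0.450, which fits less well.

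The printed figures are therefore arithmetically right for one test at uncorrected 0.05. With α shared over only two tests they would have been 0.196, 0.392 and 0.545.

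**Step 2: count the scores under the primary outcome.** Fruits (1) + vegetables (1) + vegetable categories (5) + average across FVs (1) = 8. This is a count, with fruit taken once; the article prints no number. If the correction also covers two variety scores, one Healthy Eating Index total and four energy measures, at one test each, the family is 8 + 2 + 1 + 4 = 15. That is before the sales, participation, location and subgroup tests and any strata by sex.

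**Step 3: power if the primary test is corrected.** The article names no method. The table assumes Bonferroni, so α per test is 0.05/k, and keeps the same design.

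| Tests sharing the correction (k) | α per test | Power at the exact detectable effect | Power at printed 0.17 / 0.35 / 0.48 |
|---|---|---|---|
| 1 | 0.05 | 80% | 78% / 81% / 79% |
| 2 | 0.025 | 69% | 67% / 70% / 68% |
| 3 | 0.0167 | 62% | 60% / 63% / 61% |
| 8 | 0.00625 | 45% | 43% / 46% / 45% |
| 15 | 0.0033 | 35% | 33% / 36% / 35% |
| 20 | 0.0025 | 31% | 29% / 32% / 31% |

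For k = 8 the effects detectable with 80% power become 0.24, 0.48 and 0.66, about 37% larger than stated. Holm's method tests each hypothesis at a level between 0.05/k and 0.05, so its power lies between the k = 1 row and the row for its own k.

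**Step 4: intake against percent consumed.** Amount eaten = portion served × fraction eaten. If portions in the salad bar schools shrink to a proportion p of their earlier size (p < 1) and the fraction eaten rises by a factor f with 1 < f < 1/p, percent consumed goes up while intake goes down. Which metric is primary can therefore change the sign of the result.

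**The case against.** The strongest reply is that a primary variable is named. The Design section is singular, and so is the Analyses section when it refers to the primary outcome. The sentence on scores says what will be calculated, which is a scoring statement and not a declaration of eight co-primary tests. That stands. A reader might infer eight competing primary endpoints, but the text does not say so. What remains is narrower: nothing links the named construct to one score and one unit.

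A second reply is that the correction method, the family and the testing order belong in a statistical analysis plan. That also stands, and their absence is not the complaint. The complaint is that two statements in this article disagree: power computed for one uncorrected test, and a correction applied to every test.

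A reader might also infer that any of the scores could be read at an uncorrected 0.05, so that the false-positive rate is inflated several-fold. The documents do not support this, because the Analyses section says that all tests are corrected. The exposure under the plan as written is loss of power.

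Nor do the earlier studies show vegetables rising while fruit falls. The 0.65-cup fall and the signal of higher vegetable consumption come from different studies, both in a setting where salad bars were offered alongside pre-portioned items. They show that portion size can change under self-service. They do not predict the pattern of results here.

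**Conclusion.** The point holds in a limited form. The article names one primary construct but does not tie it to one score and unit, and its 80% power applies only to a single test at uncorrected 0.05, which its own multiplicity rule does not grant to the primary test.

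That conflict is certain from the text. Its size is not, because it depends on a method and family that the article does not state. Under Bonferroni the range is 69% power for two tests down to 31% for twenty, with 45% if the eight scores form the family. The 45% should not be quoted as the trial's power. All of these figures take the plan's 16 schools, 295 lunches and ICCs as given. The correction should be made, but it does not invalidate the design: naming one uncorrected primary test restores the stated figures.

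**What to change.** State in the analysis section that the sole primary test is the between-arm difference in baseline-to-post change in total FV intake (fruit plus vegetables) per lunch, in a stated unit, at two-sided 0.05 without multiplicity correction. This follows the Design section's own wording.

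Label fruit alone, vegetables alone, the vegetable categories, percent consumed or wasted, selection and variety, diet quality and energy as secondary, and confine the correction to them. Where percent wasted is simply 100 minus percent consumed, count the two as one test.

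If the sponsor prefers to keep the primary test inside the correction, restate power and detectable effects at the corrected α.

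The Discussion reports that Year 1 and most of Year 2 have been collected and about 11,000 lunches rated. The change should therefore be dated and recorded as made after data collection began, and it should be fixed before any between-arm analysis.

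The cost is a few sentences and a dated record, with no new data. The downside is that a result in fruit alone, or in one vegetable category, can no longer be claimed as the primary result.

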As illustrated in Fig. 1 and 16 different schools will be included (A1➔D4), 4 from each sociodemographic category. In Year 1, 8 schools will be randomly selected: 4 with salad bars (A1➔D1; Intervention), matched with 4 serving pre-portioned FVs only (A2➔D2; Control). In Year 2, these 4 control schools will receive salad bars and become Intervention schools, and will be matched with 4 new, randomly selected Control schools (A3➔D3). These procedures will be repeated in Year 3, with A3➔D3 becoming Intervention schools, matched with new randomly selected Control schools (A4➔D4). There will ultimately be 12 pairs of matched schools (12 Intervention [shaded green in Fig. 1] and 12 Control [shaded yellow]).

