### Sales data

Monthly NSLP participation rates, FV sales/reimbursements, and salad bar sales/reimbursements (including whether the salad bar was part of a NSLP meal or a la carte [Intervention schools]), and number of days lunch was served per month will be obtained from the district for all selected schools.

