We will evaluate differences in dietary quality (assessed with the HEI) [57] for the total lunch and energy intake (kcals) for the total lunch, FVs, non-FVs, and beverages between Intervention and Control schools. MLM will be applied to examine the association between levels of FV intake and overall calorie consumption at lunch, both independent of school group as well as between Intervention and Control schools, to inform obesity prevention efforts.

Monthly sales (and reimbursements) and NSLP participation data will be characterized using descriptive statistics and graphical approaches. Changes in FV sales (and reimbursements) per student (based on enrollment) and % NSLP participation will be calculated (based on the total number of days lunch was served), evaluated by month. Schools will be compared on these outcomes using paired t-tests (matching on month for each school pair). Responses from cafeteria surveys and process logs will be examined to identify barriers and facilitators and implementation differences related to salad bars to inform sustainability. These variables will also be considered as potential factors explaining any differential findings between schools. Open-ended survey responses will be qualitatively examined for common themes by two independent raters, guided by thematic analysis, to identify, analyze and report themes within and across data [68]. This realistic method allows for meaning to come from participants, rather than from pre-existing codes [69].

To examine the potential differential responses to salad bars among sociodemographic groups, main effects for Title I status and race/ethnicity school group (A through D) will be examined in Aims 1 through 3 analyses. If main effects are observed, models will be stratified by sociodemographic group and moderator analyses considered as appropriate.

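### The paired t-tests for sales and NSLP participation, matched on month within school pair, make the pair-month the replicate and do not hold the 5% level

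*Protocol article*

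**What the plan says.** All from the protocol article.

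- **Data.** The Sales data section says the district will supply "Monthly NSLP participation rates, FV sales/reimbursements, and salad bar sales/reimbursements", so each school contributes several records.
- **Outcome.** The Analyses section first assigns these data to descriptive and graphical summaries. It then says that changes in FV sales per enrolled student and in percent participation "will be calculated (based on the total number of days lunch was served), evaluated by month". It does not say what the change is measured from.
- **Test.** The next sentence reads "Schools will be compared on these outcomes using paired t-tests (matching on month for each school pair"). No step reduces the months to one value per pair, and no random effect or serial-correlation term is named for these outcomes.
- **Level.** "All tests will be 2-sided at α = 0.05 level, corrected for multiple comparisons, and conducted in SAS v9.3".
- **Design.** "There will ultimately be 12 pairs of matched schools". They come from 16 schools, because after Year 1 "these 4 control schools will receive salad bars and become Intervention schools", and the same happens after Year 2. The power analysis counts "J = 16 independent schools [8 Intervention and 8 Control"].
- **The plan's own principle.** For the student-level data, the Analyses section warns: "Without accounting for correlated nature of the data, Type 1 error rate for the intervention effect might be inflated".

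**The concern.** A paired t-test treats each paired difference as an independent replicate. If the pairing is by month within a school pair, the differences number pairs times months. All months of one pair share the same two schools, so anything that moves one of them relative to the other enters several differences at once. Examples are a noisy baseline month, a staffing change or a shift in enrolment mix. The degrees of freedom are then overstated and the standard error is wrong. The Analyses section recognises this for lunches nested in schools, yet names a test that ignores it for months nested in school pairs.

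The effect of salad bars on revenue and participation is one of the questions the trial sets out to answer, and the Background section says no empirical data yet support the participation claim. A test with the wrong error rate could hand districts a spurious effect. Under one definition of change, it could instead hide a real one.

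**Working it through.** **The plan's own figure.** The article gives no power or error calculation for sales or participation. Its only figure is the minimum detectable effect for the lunch outcomes, and it reproduces. With J = 16, n = 295 and 14 df:

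MDES = (t₀.₉₇₅ + t₀.₈₀) × √{4[ICC + (1 − ICC)/n]/J}

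For ICC 0.05: (2.145 + 0.868) × √{4 × (0.05 + 0.95/295)/16} = 3.013 × 0.1153 = 0.348. The three results are 0.174, 0.348 and 0.484, against 0.17, 0.35 and 0.48 stated. That calculation counts schools as the clusters; the monthly t-test does not.

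**Inputs for the check.**
- From the documents: 12 pairs; 16 schools, hence 24 − 16 = 8 schools used in two pairs; two-sided α = 0.05.
- Assumed, because the article gives neither: the number of months per pair (m) and the correlation (r) among monthly differences of one pair.

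**Approximation.** The variance of the mean is understated by the design effect 1 + (m − 1)r. Actual Type I error is about P(|Z| > 1.96/√DE). For m = 9 and r = 0.5, DE = 1 + 8 × 0.5 = 5, and P(|Z| > 1.96/√5) = P(|Z| > 0.877) = 0.38.

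**Simulation.** There is no true effect, 20,000 runs, and pair-months are pooled in one paired t-test. Repeat runs differ by about one percentage point.

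| Scenario, 12 pairs | r = 0.1 | 0.3 | 0.5 | 0.7 |
|---|---|---|---|---|
| Independent pairs, m = 4 | 8% | 16% | 23% | 28% |
| Independent pairs, m = 9 | 14% | 29% | 39% | 47% |
| Levels, persistent school effects, re-used schools, m = 4 | 5% | 6% | 7% | 9% |
| Levels, persistent school effects, re-used schools, m = 9 | 7% | 12% | 17% | 22% |

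In the last two rows r is the share of school-month variance due to the school. A re-used school is Control one year and Intervention the next, so its effect enters with opposite signs and partly cancels.

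**How change is defined.**
- *Each month minus one shared baseline month.* Even with independent monthly errors, every difference of a pair carries the same baseline error. Then r = 1/(1 + 1) = 0.5, and simulated Type I error is 22% (m = 4) and 39% (m = 9).
- *Month-to-month change.* With independent monthly errors, successive differences are negatively correlated and Type I error is below 0.1%. Under a random walk it is about 5%.

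**One value per pair.** A t-test on 12 pair means (11 df) gives about 5% at every r tried when pairs are independent. With levels and fully persistent school effects it is conservative, at about 0.3% to 1.3% (m = 5 or 9, r = 0.3 to 0.8), because of the school overlap.

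**The case against.** The strongest reply is that the sentence can be read validly: for each calendar month, compare the two schools of every pair and run the test across pairs. That gives one value per pair and about 5% error per test. The reference to evaluation by month, the multiplicity correction and the staggered launches all fit it. This reading cannot be excluded. However, the sentence that names the test matches on month for each school pair and does not say the test is run separately by month. If that was the intention, it needs to be written. The multiplicity correction does not itself repair within-pair correlation, since it acts on p-values that are already wrong.

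A reader might also infer more than the article supports:

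- *That the test is always anti-conservative.* It is not. Under month-to-month change it can be very conservative. The direction depends on a definition the article does not give.
- *That a standing difference between two schools would be declared a salad-bar effect.* The outcomes are described as changes, and a constant difference cancels in a change. What remains is differential drift or a shared baseline.
- *That the eight re-used schools make the inflation worse.* With persistent school effects they offset it, as the table shows.
- *That only seven pairs remain after the COVID-19 closure.* The Discussion says plate-waste post-ratings were cancelled for one pair. Sales data come from the district, and the article does not say that pair's sales data were lost.

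It is also fair that these outcomes are secondary, and that they are first assigned to descriptive summaries.

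**Conclusion.** The point stands in limited form. On its plain reading, the stated test uses the pair-month as the unit although assignment is by school, and its actual error rate is not 5%. In the settings where months of a pair share a common component and pairs are independent, false positives run at about 8–28% with 4 months and 14–47% with 9. The shared-baseline definition alone gives 22% and 39%. Persistent levels bring this down to 5–9% and 7–22%, and month-to-month change can take it far below 5%. All these figures rest on assumed months and correlations, so they show the range of the problem and are not an estimate for this district. The conclusions at risk are those on sales, reimbursements and NSLP participation. The primary outcome, change in FV intake, is analysed by multilevel models and is untouched. Severity: should-fix.

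**What to change.** 1. **Define change.** For each school-year, take the mean of the post-installation months minus the mean of the pre-installation months. Use the same calendar months in both members of a pair, with the Intervention school's launch date setting the split. This gives one value per school-year.
2. **Make the school pair the unit of analysis.** The preferred form is a mixed model on the monthly data with condition by period, random pair, school and school-year effects, and small-sample degrees of freedom (for example Kenward-Roger). This also handles the schools that sit in two pairs. The simple alternative is one paired t-test on the pair values (11 df with 12 pairs). It leaves the school overlap unmodelled and may be conservative if school effects persist across years.
3. **Keep the monthly values for graphs and description.** If tests by calendar month across pairs are what was meant, say so and state how many will be run.

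The cost is analysis-plan wording on the same data. The downside is fewer degrees of freedom and wider intervals.
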